#### Concomitant interventions (treatments)

Not applicable.

### Statistical analysis

#### Datasets to be analyzed, analysis populations

The full analysis set (FAS) will include all randomized patients and will be analyzed based on the intention to treat principle.

The per protocol set will include all patients of the FAS who had complete follow-up and who did not have serious protocol violations. Patients receiving the opposite treatment than that to which they were randomized will be excluded from this set.

#### Primary analysis

The difference in recurrence rate (π_Asp_–π_placebo_) will be tested by calculating a two-sided 95% confidence interval of the difference in proportions. Inverse probability censoring weights will be used to prevent selection bias in case of many losses to follow-up. The analysis will be performed primarily on the FAS. Sensitivity analyses will be performed on the per protocol set.

#### Safety analysis

Summaries of adverse events by type and group will be prepared. Comparisons will be made between study arms for the number and types of adverse events.

#### Deviation from the original statistical plan

If substantial deviations of the analysis as outlined in this section are needed for whatever reason, the protocol will be amended. All deviations of the analysis from the protocol or from the detailed analysis plan will be listed and justified in a separate section of the final statistical report.

#### Handling of missing data and drop-outs

Missing data will be handled by the last observation performed. Sub-analysis will be performed on patients treated with concomitant blood thinners.

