### Outcomes

#### Primary study outcome measures

The primary study outcome measure is recurrence of cSDH requiring revision surgery within 6 months.

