### Statistical consideration

#### Number of participants with rationale

A systematic review by Almenawer et al. [23] reported an overall recurrence rate of approximately 10.7% for cSDH in the normal population. According to the literature, recurrence rates in the normal population range from 5% to 30% [24]. Recurrence rates have been described to reach 33% under antithrombotic therapy with ASA [12, 14]. In a retrospective study we conducted in patients where ASA treatment was continued, a recurrence rate of 22% was observed [15]. Based on the available data from the literature, we hypothesized that the recurrence rates after burr-hole drainage of cSDH under ASA treatment (π_ASA_) and without ASA treatment (under placebo, π_Placebo_) are 28% and 10%, respectively. The sample size was set to ensure at least 80% power (1 – β = 0.8), at a significance level of α = 5%. The sample size was estimated using a resampling procedure in which different sample sizes were each evaluated 999 times by drawing random samples of events based on these assumptions. This indicated that randomizing 142 patients should allow us to show the assumed difference in event rates between the groups.

The primary analysis will be performed on the full analysis set – consisting of all patients who are randomized to the study, regardless of protocol violations – and based on the intention to treat principle. The primary analysis is a comparison of incidence rate. The difference in incidence rate will be tested and a 95% confidence interval for the difference constructed. In case of many losses to follow-up, inverse probability censoring weights will be used to deal with missing outcome data. A sensitivity analysis will be performed on the per protocol analysis set. In the primary analyses, the type-I error rate for significance will be taken as α = 0.05. As secondary analysis, a time-to-event analysis will be performed comparing the hazard of recurrence between treatment arms using a Cox proportional hazards model. Secondary outcomes will be analyzed using generalized linear regression models with appropriate distribution family, depending on the outcome (binomial for binary outcome, Poisson for counts, Gaussian for continuous, normally distributed, outcomes).

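### An unrestricted last-observation rule conflicts with the weighting rule for the 6-month primary endpoint, and no text says which governs

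*Protocol article*

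**What the plan says.** The primary outcome is "recurrence of cSDH requiring revision surgery within 6 months". It is analysed on all randomized patients by intention to treat, so a patient lost before 6 months needs a rule. The article gives two.

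- **Weights, conditional.** The sample-size section says: "In case of many losses to follow-up, inverse probability censoring weights will be used to deal with missing outcome data". The Primary analysis section repeats it: "Inverse probability censoring weights will be used to prevent selection bias in case of many losses to follow-up". Neither says how much loss is many, or what is done when there is less.
- **Last observation, unconditional.** The section Handling of missing data and drop-outs says: "Missing data will be handled by the last observation performed". It names no endpoint, condition or exception.

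No section ranks these rules or confines the second to secondary outcomes. Missing 6-month outcomes are foreseeable, because for withdrawn patients the article mentions only a visit at 4–6 weeks.

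**The concern.** The problem is two stated rules that give different primary estimates from the same data, which goes beyond detail that an analysis plan could fill in. The section Deviation from the original statistical plan requires departures from the protocol to be listed and justified. An analysis plan that chose either rule would therefore still depart from a protocol sentence on the most natural reading.

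The last-observation rule is also a poor one for this endpoint. A patient lost at 6 weeks without recurrence would enter the analysis as recurrence-free at 6 months, although more than four months were never observed. Recurrences before the loss stay counted, so the error concerns only what would have happened afterwards. At stake are the size of the primary risk difference and, in a close result, whether its confidence interval excludes zero.

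**Working it through.** **Inputs from the article.** The assumed recurrence rates on ASA and placebo "are 28% and 10%, respectively". On power: "The sample size was set to ensure at least 80% power". On significance: "the type-I error rate for significance will be taken as α = 0.05". The difference is tested "by calculating a two-sided 95% confidence interval of the difference in proportions". Allocation is 1:1 with 142 patients, so 71 per arm.

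**Assumptions, because the article gives no figure.** L is the proportion lost before 6 months. s is the share of lost patients' recurrences that would fall after the loss and so go unseen.

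**1. The plan's own figure.** With unpooled variance, n per arm = (1.960 + 0.842)² × (0.28 × 0.72 + 0.10 × 0.90) / 0.18² = 70.6, rounded up to 71, or 142 in total. This matches. Exact binomial enumeration of the Wald interval test at 71 per arm gives 80.2% power. No allowance for loss is needed to reach 142.

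**2. Effect of carry-forward.** The expected rate in an arm becomes p × (1 − L × s). All powers below are by the same exact enumeration.

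| Scenario (s = 0.5) | ASA | Placebo | Difference | Power |
|---|---|---|---|---|
| No loss | 28.0% | 10.0% | 18.0 points | 80.2% |
| 15% lost per arm | 0.28 × 0.925 = 25.9% | 0.10 × 0.925 = 9.25% | 16.65 points | 76.2% |
| 20% lost on ASA, 5% on placebo | 0.28 × 0.90 = 25.2% | 0.10 × 0.975 = 9.75% | 15.45 points | 69.7% |
| 5% lost on ASA, 20% on placebo | 0.28 × 0.975 = 27.3% | 0.10 × 0.90 = 9.0% | 18.3 points | 83.1% |

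Equal loss pulls the difference toward zero. Unequal loss moves it down or up, depending on which arm loses more.

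**3. The fair comparator for power.** Loss costs power under any method. At 15% loss per arm, complete cases (about 60 per arm, 28% against 10%) have 74.4% power, so carry-forward at 76.2% is no worse. At 20% on ASA and 5% on placebo, complete cases (about 57 and 67) have 74.9%, against 69.7% for carry-forward.

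**4. Range over s.** At 15% loss per arm:

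| s | Difference: 18 × (1 − 0.15 × s) | Power |
|---|---|---|
| 0.1 | 17.7 points | 79.5% |
| 0.25 | 17.3 points | 78.3% |
| 0.5 | 16.65 points | 76.2% |
| 1.0 | 15.3 points | 71.7% |

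**5. Can the choice of rule change the conclusion?** These are illustrative data with Wald intervals. No lost patient had a recurrence before loss. The available-case result stands in for weights without covariates, where lost patients contribute no follow-up.

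| Data | Carry-forward (95% CI) | Available-case (95% CI) |
|---|---|---|
| 14 v 6 events, 14 lost per arm | 14/71 − 6/71 = 11.3 (−0.02 to 22.6) | 14/57 − 6/57 = 14.0 (0.3 to 27.8) |
| 17 v 7 events, 4 lost on ASA and 14 on placebo | 17/71 − 7/71 = 14.1 (2.0 to 26.2) | 17/67 − 7/57 = 13.1 (−0.4 to 26.6) |

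In the first row only the available-case interval excludes zero. In the second only the carry-forward interval does.

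**The case against.** The strongest reply is that the rules can be reconciled. The weights are assigned specifically to the primary outcome, while the last-observation sentence is generic and comes after the secondary and safety analyses. One might read it as covering only the clinical scales, or as the rule when losses are few. It also never uses the term carry-forward. It follows that a reader should not call the rules logically incompatible. But the article states none of these reconciliations, and under the second the switch point is still undefined.

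A threshold for many losses could sit in an unshown analysis plan. A reader might infer that the trigger invites choosing the estimator by its result. The document does not support this: the amount of loss can be judged without arms or outcomes, and nothing says otherwise. What stands is that a conditional estimator is unnecessary, because one method can cover any amount of loss.

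There are safeguards. The per-protocol set requires complete follow-up, and the secondary Cox model can censor lost patients. Both would help to expose a carry-forward distortion, but neither settles what the primary estimate is.

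Three stronger inferences fail.

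- That carry-forward counts every lost patient as recurrence-free: recurrences before loss remain events.
- That it cuts power from 80% to 76% at 15% equal loss: that compares it with no loss at all.
- That it seriously inflates false positives: with both true rates at 19% and 20%/5% loss, half unseen, the spurious difference is 19 × 0.90 − 19 × 0.975 = −1.4 points, and the rejection rate moves only from 5.1% to 5.6%.

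**Conclusion.** The point holds as a conflict between two stated rules with no precedence, one of which gives a biased 6-month recurrence rate. The bias in each arm's rate is downward. The difference is biased toward zero under equal loss and in either direction under unequal loss.

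The size is modest when loss is balanced: about 1.3 points off an 18-point difference at 15% loss, with no real power cost beyond the loss itself. It is larger when more ASA patients are lost: about 2.5 points off at 20% against 5%, with power near 70%. These sizes rest on assumed loss rates and on half of the lost patients' recurrences going unseen. A fourfold imbalance in loss may be unlikely in a double-blind trial. It should still be corrected before analysis, because the rule governs the primary estimate and a borderline result could turn on it.

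For the clinical scales, a reader might infer that an early postoperative score would always stand in for the 6-month score. The document does not support that: the scales are also recorded at 4–6 weeks, so a patient missing only the last visit would carry that value.

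**What to change.** 1. Delete the last-observation sentence, or at least exclude the primary endpoint from it.
2. State one primary estimator that applies at any level of loss: the 6-month risk difference on the full analysis set with inverse probability censoring weights. With nobody lost, this equals the plain difference in proportions.
3. Remove the condition about many losses from both the sample-size section and the Primary analysis section.

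The cost is wording, a little programming and a slightly less simple primary estimator. No extra patients are needed.

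Optional additions are a tipping-point sensitivity analysis for the primary endpoint and a likelihood-based or multiple-imputation method for the clinical scales. Resolving the conflict does not depend on them.

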#### Monitoring

The electronic CRF (e-CRF) and source data will be reviewed for completeness and accuracy through regular monitoring provided by the study site. The study staff will be available for the monitoring visits in order to give access to the study files and provide any kind of support needed. The service will be provided by the Monitoring Department of CTU Basel.

#### Audits and inspections

Inspections by regulatory authorities during the study or following study completion are performed to ensure proper study conduct and data handling procedures according to International Conference on Harmonisation Good Clinical Practice guidelines and regulatory requirements. Inspections may include verification of all source documents, e-CRF, site files, and a visual inspection of the study site. Direct access to all documents and sites involved in the study will be provided by the study staff members. In case of an announced inspection, immediate notification of the other party is necessary.

#### Confidentiality, data protection

Direct access to source documents will be permitted for purposes of monitoring. The participants name or other personal identifiable data are not recorded in the CRF or the e-CRF. Subject confidentiality will be ensured by utilizing unique identification numbers for the corresponding data. Each participant will be coded by a number during the screening. After electronic enrolment to the study, the participant will be assigned with a unique personal study number (patient ID). All data collected for the study will be entered under the patient ID only.

The relation between the patient ID and participant’s name, address, date of birth and screening number will be documented in a written register (‘patient identification list’). The patient identification list will be stored in the research study office of the department of Neurosurgery, University Hospital of Basel. The Sponsor, Principal Investigator, Co-Investigator and study nurses will have access to the protocol and dataset, while the CTU statistician will have access to the statistical codes during and after the study.

Study data entered into the EDC system is only accessible by authorized persons. Once the data of all subjects is transferred to the EDC system, the database will be locked and closed for further data entry. The complete study dataset is exported, encrypted and transferred to the principal investigator through a secured channel by the responsible Data Manager at CTU Basel.

#### Follow-up of (serious) adverse events

Patients with reported serious adverse events during hospitalization will stay in hospital until the matter is resolved. If an intracranial bleeding has been diagnosed (and in some cases operated on), patients will be followed up in our outpatient clinic. NE (GCS, GOS, mRS and Markwalder score) as well as CT scan findings will be documented at 4–6 weeks and at 6 months postoperatively. Events other than those of a neurosurgical nature (thrombotic, etc.) will be followed up in a department in our hospital (e.g., cardiology) for as long as needed.

### Data entry/coding/security and storage

#### Case report forms

For each subject included in this study, a CRF will be completed, dated and signed by the study investigator. Each CRF will be kept current to reflect the participant status at each phase during the course of the study. All participants receive a unique identification number (patient ID) and no person-identifying data, such as name or initials, are collected in the CRF.

#### Specification of source documents

The investigator will maintain source documents for each patient included in the study, consisting of the paper CRF forms, case and visit notes (hospital or clinical medical records) containing demographic and medical information, laboratory data, electrocardiograms, and the results of any other tests or assessments.

#### Record keeping/archiving

All study data, including CRFs, Trial Master Files, and informed consent forms, will be archived for a minimum of 10 years after study termination or premature termination of the clinical trial. The study data will be archived in the research office of the Department of Neurosurgery University Hospital of Basel.

#### Data management

The study data recorded in the CRF will be transferred to a corresponding e-CRF by authorized persons (see Staff List).

#### Data management system

The e-CRF will be implemented by the responsible Data Manager at CTU Basel using the EDC software SecuTrial. The EDC software runs on a server maintained by the IT-department at University Hospital Basel.

#### Electronic and central data validation

Data entered into the e-CRF will be validated for completeness and discrepancies automatically. The data will be reviewed by the responsible investigator as well as by an independent monitor. The monitor will raise queries using the query management system implemented in SecuTrial. Designated investigators have to respond to the query and confirm or correct the corresponding data. Thereafter, the monitor can close the query.

#### Monitoring

The e-CRF and source data will be reviewed for completeness and accuracy through regular monitoring provided by the study site. The study staff will be available for the monitoring visits in order to allow access to the study files and provide any kind of support needed. The service will be provided by the Monitoring Department of CTU Basel.

#### Confidentiality, data protection

The Sponsor, Principal Investigator, Co-Investigator and study nurses will have access to the protocol and dataset. While the CTU statistician will have access to the statistical codes during and after the study.

Study data entered into the EDC system is only accessible by authorized persons. Once the data of all subjects is transferred to the EDC system, the database will be locked and closed for further data entry. The complete study dataset is exported, encrypted and transferred to the principal investigator through a secured channel by the responsible Data Manager at CTU Basel.

#### Ethical conduct of the study

The study will be performed in accordance to the protocol and with principles enunciated in the current version of the Declaration of Helsinki, the guidelines of Good Clinical Practice issued by the International Conference on Harmonisation and the Swiss Law and Swiss regulatory authority’s requirements.

#### Patient information and informed consent

The investigators will explain to each participant the nature of the study, its purpose, the procedures involved, the expected duration, the potential risks and benefits, and any discomfort it may entail. All participants eligible for the study will be provided a participant information sheet and a consent form describing the study and providing sufficient information for them to make an informed decision about their participation in the study. The study population includes vulnerable participants. If patients are not capable of judgement (e.g., dementia/neurologic state) an informed consent of the next-of-keen and an independent physician will be obtained. If, in case of emergency, the next-of-keen is not available, informed consent will be obtained from an independent physician on site.

#### Participant privacy and confidentiality

The investigator affirms and upholds the principle of the participant’s right to privacy and that they shall comply with applicable privacy laws. Especially, anonymity of the participants shall be guaranteed when presenting the data at scientific meetings or publishing them in scientific journals.

Individual subject medical information obtained as a result of this study is considered confidential and disclosure to third parties is prohibited. Subject confidentiality will be further ensured by utilizing subject identification code numbers to correspond to treatment data in the computer files. For data verification purposes, authorized representatives of the Sponsor-Investigator, a competent authority (e.g., Swissmedic), or an ethics committee may require direct access to parts of the medical records relevant to the study, including participants’ medical history.

#### Early termination of the study

The Sponsor-Investigator may terminate the study prematurely according to certain circumstances, for example, ethical concerns, insufficient participant recruitment, when the safety of the participants is doubtful or at risk, alterations in accepted clinical practice that make the continuation of a clinical trial unwise, or early evidence of benefit or harm of the experimental intervention.

#### Protocol amendments

Substantial amendments are only implemented after the respective approvals of the competent ethics commitée (CEC) and competent authority (CA). Under emergency circumstances, deviations from the protocol to protect the rights, safety and well-being of human subjects may proceed without prior approval of the sponsor and the CEC/CA. Such deviations shall be documented and reported to the sponsor and the CEC/CA as soon as possible. All non-substantial amendments are communicated to the CA as soon as possible if applicable and to the CEC within the Annual Safety Report.

## Discussion

The continuation of ASA treatment during intracranial surgery might lead to perioperative bleeding complications such as higher perioperative blood loss, intracerebral bleeding, recurrent hematoma with or without neurologic deficits, or anemia. However, the risk of bleeding whilst operated under ASA is not well researched or documented in neurosurgical patients. On the other hand, discontinuation of ASA can lead to perioperative thromboembolic complications such as myocardial infarction, stroke, transient ischemic attack, PMI, embolic arterial occlusion of an extremity, or deep vein thrombosis. Data analyzing the rates of thromboembolic complications due to discontinuation of ASA treatment in the perioperative period are equally sparse.

To date, there is still no evidence-based consensus on how to treat patients undergoing burr-hole drainage of cSDH who are under ASA treatment. Therefore, this study will be of very high value for patients and physicians and will significantly improve our knowledge on the topic.

### Limitations

Although this is a randomized, double-blinded, placebo-controlled study, it has some limitations. Since burr-hole drainage is preformed either as an emergency or elective procedure, pre- and postoperative discontinuation time of ASA differs between the patients. By assuring that all patients under placebo will discontinue ASA at least 7 days after surgery, this bias should be minimal. Patients are often discharged before the study medication is sustained, and therefore compliance of the intake cannot be guaranteed in all patients. In order to minimize this bias, we will collect the empty medication boxes at the first follow-up visit. We expect the study to be multicentric by the first quartal of 2019, which will definitely lead to an improvement in the study quality.

#### Trial status

Version 2, 23.02.2017.

Recruitment beginning: 03/2018.

Recruitment end: 03/2022.

## Abbreviations

ASA: acetylsalicylic acid
BP: blood pressure
CA: competent authority
cCT: cranial computer tomography
CEC: competent ethics commitée
CTU: Clinical Trial Unit
CRF: case report form
cSDH: chronic subdural hematoma
ECG: electrocardiogram
e-CRF: electronic case report form
EDC: electronic data capture
FAS: full analysis set
GCS: Glasgow Coma Score
GOS: Glasgow Outcome Scale
HR: heart rate
INR: international normalized ratio
MLS: midline shift
mRS: modified Rankin scale
NE: neurologic evaluation
PMI: perioperative myocardial injury
SAT: oxygen saturation
